#### Barratt Impulsiveness Scale

This 30-item self-report questionnaire assesses impulsive personality traits (Patton et al., 1995). A form of this measure that is sensitive to changes in impulsivity over time (Ghahremani et al., 2013) will be used.

#### Stop-Signal Task

On “go” trials, a series of visual stimuli are presented to prompt pressing a left or right corresponding key. On “stop” trials (i.e., 25% of all trials), a tone (i.e., a “stop-signal”), will be presented after a short delay after the “go” stimulus (this delay is termed the stop-signal delay; SSD); this “stop-signal” will indicate to the participant that they should withhold responding. The SSD is adjusted on a trial-by-trial basis according to performance. The primary dependent variable, stop-signal reaction time, is the mean difference between the SSD and the reaction time to “go” stimuli, and indicates how quickly the participant can inhibit an ongoing motor response.

#### Monetary Choice Questionnaire

Participants must select between one of two hypothetical options in 27 questions to receive a certain amount of money immediately or a larger amount later. The discrepancies between the monetary amounts and duration of the delay are varied across questions. A hyperbolic statistical function is fit to the data to estimate the individual’s point of indifference between the options. The primary dependent variable is the indifference point, or total k value, determined from the participant’s selections across the task. Scores are typically adjusted with the natural log to compensate for skew (Kirby et al., 1999).

#### Toronto Alexithymia Scale-20

Emotional self-awareness will be assessed using the Toronto Alexithymia Scale-20 (TAS-20; Bagby et al., 1994), a widely used questionnaire that consists of three subscales that provide scores for corresponding factors. Two of the factors assess emotional self-awareness: Factor 1: Difficulty Identifying Feelings; and Factor 2: Difficulty Describing Feelings. Factor 3 assesses Externally-Oriented Thinking. TAS-20 total score (the sum of the three subscale scores) is interpreted as follows: 0–51: no alexithymia; 52–60: possible alexithymia; 61 and above: alexithymia (Taylor et al., 1999).

#### Difficulties in Emotion Regulation Scale

Difficulties in Emotion Regulation Scale (DERS) will be administered to assess an emotion dysregulation (Gratz and Roemer, 2004). This 36-item questionnaire is divided into six-distinct subscales: Non-acceptance of Emotional Responses (NON-ACCEPT); Difficulties Engaging in Goal-Directed Behavior (GOALS); Impulse Control Difficulties (IMPULSE); Lack of Emotional Awareness (AWARE); Limited Access to Emotion Regulation Strategies (STRATEGIES); and Lack of Emotional Clarity (CLARITY). Scores on each subscale can be summed to create a total score which can range from 30 to 180; higher scores represent more difficulties in emotion regulation.

#### Beck Depression Inventory and Beck Anxiety Inventory

The Beck Depression Inventory (BDI) (Beck et al., 1996) and Beck Anxiety Inventory (BAI) (Beck et al., 1988) are self-report inventories to verify depressive and anxiety symptoms respectively. They will be employed to verify exclusion criteria and monitor potential adverse event related to drug administration.

### Data Analytic Plan

#### Power Considerations

A sample size was selected based on a power analysis that was performed previously. Eighteen subjects per group is assumed to be necessary to provide sufficient power (β > 0.8) to detect interaction effects as small as *f* = 0.2, assuming a within-subject correlation coefficient of 0.8 based on previous study (Alakurtti et al., 2015) for the repeated measures and two-sided significance of α = 0.05. Taking into account the potential drop out from the study of roughly 10% of all recruited participants, we set a sample size of *N* = 40. A previous study that aimed to show D2-type receptor upregulation in humans after completion of an exercise intervention revealed a group-by-time interaction on the dependent variable to the magnitude of *f* = 0.28 (Robertson et al., 2016). Thus, the current study appears to be powered to detect a significant effect in our main aim.

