### Random Allocation

Participants will be randomly assigned in a 1:1 manner using a stratified block-randomization procedure with age as the stratification factor. The allocation sequence has been computer-generated and will be carried out by a study statistician who is not involved in any other study procedures in order to preserve the double-blind design. A blinded stratification list, including subject ID and age will be used to assign participants a group based on the stratification factor (i.e., active or placebo). A study pharmacist in charge will match this information to the unblinded stratification list and fills the prescription. The pharmacist is the only person who will have access to the unblinded stratification list.

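### At its stated inputs the sample-size paragraph's 18 per group gives about 96% power, and 80% needs only 11 per group, so the power target or another input is misreported

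*Protocol article*

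**What the plan says.** The Power Considerations section of the protocol article gives the only quantitative basis for the size of the trial. It states: "Eighteen subjects per group is assumed to be necessary to provide sufficient power (β > 0.8) to detect interaction effects as small as". The effect size that completes this sentence is f = 0.2. The calculation is described as "assuming a within-subject correlation coefficient of 0.8 based on previous study", and the test level is given as "two-sided significance of α = 0.05". The section then allows for roughly 10% drop-out and sets N = 40. It cites an interaction of f = 0.28 from an earlier exercise intervention study and concludes: "Thus, the current study appears to be powered to detect a significant effect in our main aim".

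Other sections fix the rest of the calculation. Under Random Allocation, "Participants will be randomly assigned in a 1:1 manner". Under Statistical Analysis, the Aim 1 hypothesis is tested by the group-by-time interaction in a two-group comparison with one pre- and one post-intervention measurement. The article does not say how f is defined.

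**The concern.** The paragraph makes two claims that can be checked from its own numbers: that 18 per group is what power above 0.8 requires, and that f = 0.2 marks the lower end of what the trial can detect. If the inputs are as stated, the paragraph should return 18 per group for about 0.8, and it does not. A reader then cannot tell what power the trial was designed for, or which input behind N = 40 was actually used. The N matters because each healthy volunteer has two radiotracer scans. The symbol is also wrong: "sufficient power (β > 0.8") uses the letter that conventionally denotes the type II error.

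**Working it through.** **Inputs**

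- Size: 18 per group, N = 36 completers (Power Considerations).
- Effect: f = 0.2 for the interaction (Power Considerations).
- Within-subject correlation: ρ = 0.8 (Power Considerations).
- Alpha: 0.05, two-sided (Power Considerations).
- Allocation: 1:1 (Random Allocation).
- Repeated measures: m = 2, in k = 2 groups (Statistical Analysis).
- Assumption: f is on the standard repeated-measures scale, on which ρ enters the noncentrality. The article does not state this, but it is the scale on which a stated ρ is needed.

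**Formula.** The interaction F test has 1 and N − 2 degrees of freedom and noncentrality λ = f² × N × m / (1 − ρ).

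**The plan's own figure.** λ = 0.04 × 36 × 2 / 0.2 = 14.4 on 1 and 34 df. Power = 0.958.

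**Cross-check as a t test on change scores.** On this scale f = 0.2 is a between-group difference in change of 0.8 SD. The SD of change is √(2 × (1 − 0.8)) = 0.632 SD, so its variance is 0.4. Then λ = 0.8² / (0.4 × 2/18) = 0.64 / 0.0444 = 14.4, as before. Spending one degree of freedom on a covariate leaves power at 0.9575.

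**Size needed at the stated inputs**

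| n per group | N | λ | Power |
|---|---|---|---|
| 10 | 20 | 8.0 | 0.763 |
| 11 | 22 | 8.8 | 0.806 |
| 17 | 34 | 13.6 | 0.947 |
| 18 | 36 | 14.4 | 0.958 |
| 20 | 40 | 16.0 | 0.974 |

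The smallest size is 11 per group for 80% power, 15 for 90% and 18 for 95%.

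**Smallest effect detectable with 36 completers.** Solving for power 0.80 at ρ = 0.8 gives f = 0.152 (λ = 0.152² × 36 × 2 / 0.2 = 8.3), not 0.2.

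**Other calculations tried at f = 0.2, ρ = 0.8**

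| Variant | Smallest n per group for 80% |
|---|---|
| One-sided alpha | 9 |
| One covariate df | 11 |
| λ without the factor m | 21 |
| ANCOVA on a 0.4 SD post-treatment difference | 37 |
| No correlation term | 51 |

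None returns 18 per group at 80%.

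**Sensitivity to the correlation (N = 36, f = 0.2)**

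| ρ | λ | Power |
|---|---|---|
| 0.8 | 14.4 | 0.958 |
| 0.7 | 9.6 | 0.853 |
| 0.6 | 7.2 | 0.741 |
| 0.5 | 5.76 | 0.645 |

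**Drop-out step.** 36 / 0.9 = 40. This reproduces, so the discrepancy lies in the core calculation or its description.

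**The case against.** The strongest reply is that the text gives a floor, not a target of 80%, and 0.958 is above the floor. That stands: the bare assertion that 18 per group gives more than 0.8 power at f = 0.2 is true. What does not survive is the claim of necessity, since 11 per group also clears the floor, or the description of f = 0.2 as the lower end of the detectable range.

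A second reply is that the authors may have run the calculation for 95% power. This fits every other stated number, because 18 per group is exactly the minimum for 95%. It is an inference, and if it is right, the power target is the misreported input.

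A third is that the β label is only a slip. That also stands. The word power comes directly before it, so nobody should read it as power below 0.2, but it should be corrected.

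A reader might go further in four directions that the documents do not support:

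- **That power could be as low as about 0.21.** This follows if f is on the partial-eta-squared (change-score) scale. On that scale the correlation is already absorbed and would not be an input, yet the paragraph gives ρ = 0.8 as a working assumption.
- **That the correlation actually used was about 0.65.** That value would return 18 per group at 80% power, but nothing in the text points to it.
- **That a null result could not be interpreted.** A null result is read from the estimate and its confidence interval, which do not depend on this paragraph. On the best-supported reading the trial has more power than the floor it claims.
- **That the comparison with f = 0.28 is invalid.** Whether that figure is on the same scale depends on a source not shown. On the standard scale with ρ = 0.8, 36 completers have power of 0.999 for it.

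**Conclusion.** The point holds as a reporting error in the sample-size justification. At the stated inputs, 18 per group gives about 96% power, 80% needs 11 per group, and 36 completers have 80% power at f of about 0.15. The statement that 18 per group is required for power above 0.8 at effects down to f = 0.2 is therefore wrong as written. Either the power target was misreported, with 95% the value that fits, or another input differs from the one used.

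The conclusion rests on f being on the standard repeated-measures scale and on a two-group, two-time-point interaction test. If ρ = 0.8 holds, the size is generous for f = 0.2. If ρ is lower, the margin shrinks, and at ρ = 0.6 or below power is under 0.8. The point does not show that N = 40 is too small or that the design or analysis must change.

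**What to change.** Keep N = 40 and restate the paragraph after checking the power analysis that was run.

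- If the stated inputs are right, write for example: 36 completers give 1−β = 0.96 for f = 0.2, or 0.80 for f of about 0.15 (0.152), at a within-subject correlation of 0.8 and two-sided alpha of 0.05. If the target was 95%, say so.
- If an input differed from the one used, correct that input instead.
- Replace β with 1−β.
- State the f convention, namely that the correlation enters through λ = f² × N × m / (1 − ρ).
- Add one sensitivity line: at f = 0.2 with 36 completers, power is about 0.85 at ρ = 0.7 and 0.65 at ρ = 0.5.

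The cost is rewording one paragraph. Enrolment, design and analysis stay as they are.

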#### Statistical Analysis

We will use graphical and numerical summaries to screen the data for outliers and violations of model assumptions. For Aim 1, the hypothesis will be tested by evaluating the effects of treatment group (istradefylline vs. placebo), time (pre- vs. post-intervention), and the group-by-time interaction on D2-type BP_ND_ (which will be the dependent variable) using a repeated measures ANCOVA. In *post hoc* tests, the effect of time will be tested using paired *t*-tests in each group to identify the sign of any interaction effect. For Aim 2a, the hypothesis will be tested by using the same above-defined ANCOVA model but with cognitive measures as the dependent variable instead of D2-type BP_ND_. For aim 2b, partial correlation analysis will be performed to evaluate the potential associations between change in BP_ND_ and change in cognitive measures. These statistical analyses will be conducted using SPSS IBM 19 (IBM, Armonk, NY, United States).

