The main research aim of this study will be to determine whether medium-term (i.e., 2-week) administration of istradefylline can produce upregulation of dopamine D2 receptors in humans (Aim 1). It is hypothesized that participants who receive 2-week administration of istradefylline, as compared to placebo, will exhibit increased dopamine D2-type receptor BP_N__D_ as indicated by a significant group (istradefylline vs. placebo) × time (pre- vs. post-intervention) interaction (Hypothesis 1). The secondary aims will be to assess the effects of istradefylline on cognitive measures (Aim 2a), and to evaluate the extent to which any effects on cognition are related to changes in BP_ND_ (Aim 2b). Therefore, the secondary hypotheses are that istradefylline administration would improve cognitive performance more than placebo administration (as indicated by a significant group × time interaction; Hypothesis 2a), and that any effects of istradefylline administration on D2-type receptor BP_ND_ will be associated with such effects on cognitive performance (Hypothesis 2b).

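### The group-by-time test for Aims 1 and 2a is a change-score comparison unless baseline is entered as a covariate; adjusting for baseline is a modest gain in precision at almost no cost

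*Protocol article*

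**What the plan says.** The Introduction defines Hypothesis 1 as a significant interaction of group with time, and Hypothesis 2a likewise for cognition. Under Statistical Analysis, Aim 1 is tested by the effects of group, time and "the group-by-time interaction on D2-type BP_ND_ (which will be the dependent variable) using a repeated measures ANCOVA". Time has two levels, before and after the intervention, so baseline BP_ND is one of the two values of the outcome. Aim 2a is tested by "using the same above-defined ANCOVA model but with cognitive measures as the dependent variable". The model is called an ANCOVA, but no covariate is named for it.

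Under Random Allocation, participants are assigned "using a stratified block-randomization procedure with age as the stratification factor". Statistical Analysis does not mention age.

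Power Considerations sets 18 per group "to detect interaction effects as small as *f* = 0.2", "assuming a within-subject correlation coefficient of 0.8" and "two-sided significance of α = 0.05". The correlation comes from a previous study, the same one that the PET section cites for test-retest reliability of the scan.

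**The concern.** With only two time points and no baseline covariate, the interaction test is the t-test on post minus pre. That test subtracts the whole baseline difference between the arms, whereas regression on baseline subtracts only the share that baseline predicts. When the pre-post correlation is below 1, the change score therefore carries baseline noise that adjustment would remove. With 18 to 20 per arm, some chance baseline difference is to be expected.

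At stake is the width of the confidence interval, and so power, in a small trial. The loss grows as the correlation falls. The only correlation in the document is for the PET outcome, yet the same model serves the questionnaires and the stop-signal task.

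**Working it through.** **Inputs.** From Power Considerations: f = 0.2, ρ = 0.8, two-sided α = 0.05, N = 36 completers (18 per arm). Equal variance before and after is assumed, and effects are in units of that common SD.

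**1. The plan's own figure.** The usual noncentral F for a two-group, two-time interaction has λ = f²·N·2/(1−ρ) = 0.04 × 36 × 2/0.2 = 14.4 on 1 and 34 df. Power is 0.958. The stated power above 0.8 is thus true as an inequality, but 18 per group is not the size that 80% power requires: 22 in total would do, and 36 is the N for 95% power. Under the other common convention, λ = f²·N/(1−ρ) = 7.2, power is 0.741, and 80% power needs 42. Neither convention gives 36 at 80%. That is a separate matter. Both conventions are carried below.

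**2. The interaction is the change-score test.** On simulated data with 18 per arm and no covariate, the interaction F was 10.4948 and the squared t on change scores was 10.4948.

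**3. Variance of the treatment effect.** Change score: proportional to 2(1−ρ) = 0.40. Baseline-adjusted: proportional to 1−ρ² = 0.36. The ratio is (1+ρ)/2 = 0.90, so the standard error is about 5% smaller. Estimating the baseline slope multiplies the adjusted variance by 1 + 1/(N−4) = 1 + 1/32 = 1.031. Net ratio: 0.90 × 1.031 = 0.928, a reduction of about 7%.

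**4. Power at the plan's inputs.** Under the usual convention, f = 0.2 is a difference in change of D = 0.8 SD, since 0.8² × 9/0.40 = 14.4. Adjusted: λ = 0.8² × 9/0.36 = 16.0, and 16.0/1.031 = 15.5 on 1 and 33 df.

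| Convention | Change score | Baseline-adjusted |
|---|---|---|
| λ = f²·N·2/(1−ρ) | 0.958 | 0.969 |
| λ = f²·N/(1−ρ) | 0.741 | 0.771 |

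Ten thousand simulated trials gave 0.955 and 0.970 for the first row, and 0.740 and 0.771 for the second.

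**5. Other correlations** (assumed values, f = 0.2, N = 36, usual convention, net of slope estimation):

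| ρ | Variance ratio | Net ratio | Power, change | Power, adjusted |
|---|---|---|---|---|
| 0.5 | 0.75 | 0.773 | 0.645 | 0.755 |
| 0.6 | 0.80 | 0.825 | 0.741 | 0.818 |
| 0.7 | 0.85 | 0.877 | 0.853 | 0.895 |
| 0.8 | 0.90 | 0.928 | 0.958 | 0.969 |
| 0.95 | 0.975 | 1.005 | 1.000 | 1.000 |

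At ρ = 0.95 the net gain is nil.

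**6. Adding age.** Its gain cannot be computed, because the document gives no association of age with BP_ND or with its change. As a cautious bound, suppose age explained nothing and were balanced only by chance. The factor becomes 1 + 2/(N−5) = 1 + 2/31 = 1.065, the net ratio at ρ = 0.8 is 0.90 × 1.065 = 0.958, and power is 0.964 on 1 and 32 df. Stratified allocation should make the true cost smaller.

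**The case against.** The best defence is that the plan is coherent and valid. Hypothesis, sample size and test all use the same interaction. Under randomisation the change-score comparison is unbiased and keeps its type I error. All of that stands, so a reader who infers a biased or invalid primary test goes too far.

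Three further inferences are tempting and also go too far.

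- *Baseline cannot be a covariate here because it is already an outcome.* This is not so. Regressing the change on group and baseline gives exactly the same group test as regressing the post value on group and baseline. A repeated measures ANCOVA with baseline crossed with time would therefore be the recommended analysis. The document does not say that this is what is meant.
- *The model excludes age, and so loses precision.* The term ANCOVA implies some covariate, and a condensed article may leave the list to the full protocol or analysis plan. Moreover, any age effect on the level of BP_ND cancels in post minus pre. Only an age effect on the change would matter, and the document gives no figure for one.
- *Adjustment recovers the whole drop-out allowance.* The ratio 0.90 suggests so (36/0.90 = 40), but the net ratio gives 36/0.928 = 38.8.

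The objection that the gain is small at the plan's own inputs is also right: about one power point, or three under the less favourable convention. What it does not remove is that the stated terms are group, time and their interaction, and that a more efficient analysis of the same data is available.

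**Conclusion.** The point holds as one of efficiency, not validity. As written, and unless baseline is entered as a covariate crossed with time, Aims 1 and 2a rest on change-score comparisons. For BP_ND at ρ = 0.8 the cost is about 10% of variance, about 7% net at 36 completers, and power of 0.958 instead of 0.969. For the cognitive measures it could reach about 8 to 11 power points, but only on the assumption of a correlation of 0.5 to 0.6 and the same f of 0.2. The document supplies neither for those measures.

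The figures rest on equal pre and post variances and a common linear baseline slope. The case for age is that randomisation is stratified by it and Statistical Analysis does not name it. No precision gain is claimed for it.

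**What to change.** State the primary analysis as an ANCOVA of post-intervention BP_ND on treatment group, with baseline BP_ND and age (the stratification factor) as covariates, and report the adjusted group difference with its 95% confidence interval. Use the same form for each Aim 2a measure with that measure's own baseline. Keep the group-by-time test as a sensitivity analysis, so that Hypotheses 1 and 2a can still be read in their stated form.

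The cost is two covariate degrees of freedom and a change of wording, which must be fixed before unblinding. Baseline values and age are already part of the data to be collected, so no visit, measurement or participant is added.

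### The direction of the group-by-time interaction is assigned to paired t-tests within each group, which do not compare the groups and can leave the sign undetermined

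*Protocol article*

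**What the plan says.** The Introduction of the protocol article states a directional, comparative hypothesis: BP_ND will increase on istradefylline relative to placebo, "as indicated by a significant group (istradefylline vs. placebo) × time (pre- vs. post-intervention) interaction (Hypothesis 1". Under Statistical Analysis, Aim 1 is tested through the effects of group, time "and the group-by-time interaction on D2-type BP_ND_ (which will be the dependent variable) using a repeated measures ANCOVA". The post hoc step follows: change over time is examined by paired t-tests "in each group to identify the sign of any interaction effect". Aim 2a reuses the ANCOVA model with the cognitive measures as outcomes. The text does not say whether the paired t-tests are reused as well. The article names no between-group contrast as the source of the direction.

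Under Power Considerations, 18 per group is described as "necessary to provide sufficient power (β > 0.8"), "to detect interaction effects as small as *f* = 0.2", with a within-subject correlation of 0.8 and a "two-sided significance of α = 0.05".

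**The concern.** The interaction test is two-sided, so a significant result still has to be given a direction before it can support Hypothesis 1. The plan gives that job to two tests, neither of which compares the arms. Each asks whether one arm's mean change differs from zero, and a pair of such p-values is not a treatment comparison.

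At stake is how the primary result is read. A significant interaction may come with two non-significant paired tests, or with two significant tests pointing the same way. In either case the significance pattern does not show which arm gained more. There is also a risk that the write-up leans on a contrast of the type significant on drug, not significant on placebo. The Discussion faults an earlier caffeine PET study for being a plain before-after comparison and gives this as a reason to randomise. Reading direction from before-after tests in each arm sits badly with that reasoning.

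**Working it through.** **Inputs from Power Considerations.** Interaction f = 0.2, correlation 0.8, two-sided alpha 0.05, 18 evaluable per group (36 in total), dropout about 10%. Changes below are in units of the between-subject SD at one time point.

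**The plan's own figure.** For a 2 × 2 within-between interaction, λ = f² × N × m/(1 − ρ) = 0.04 × 36 × 2/0.2 = 14.4, with 1 and 34 df. Power is 0.958, so the claim of more than 0.8 is true as an inequality. (The smallest total N for power 0.80 is 22. That mismatch is separate and does not bear on this point.) Dropout: 36/0.9 = 40, as stated.

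**What the interaction is.** f = 0.2 corresponds to a difference in mean change of 4f = 0.8 SD. The SD of change is √(2 × (1 − 0.8)) = 0.632 SD.
- Between-group contrast: SE = 0.632 × √(2/18) = 0.211. The 95% CI half-width is 2.03 × 0.211 = 0.43. An observed difference of 0.8 therefore has a CI of about 0.37 to 1.23.
- One arm alone: SE = 0.632/√18 = 0.149. With 17 df the paired test needs a mean change of about 2.11 × 0.149 = 0.31 to be significant.

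A difference of 0.43 is thus enough for the interaction, but split evenly it is about 0.21 per arm, short of 0.31. A significant interaction with two non-significant paired tests is therefore quite possible.

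**How often each pattern occurs.** Simulation of normal change scores, 18 per group, 100,000 trials per scenario. The pattern columns are percentages of trials with a significant interaction.

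| True mean change, istradefylline / placebo | Interaction significant | Drug only | Placebo only | Both, opposite directions | Both, same direction | Neither |
|---|---|---|---|---|---|---|
| +0.8 / 0 | 95.7% | 95.7 | 0.0 | 2.6 | 1.7 | 0.0 |
| +0.4 / −0.4 | 95.8% | 20.8 | 20.8 | 53.4 | 0.0 | 4.9 |
| 0 / −0.8 | 95.8% | 0.0 | 95.7 | 2.6 | 1.7 | 0.0 |
| +1.2 / +0.4 | 95.8% | 29.6 | 0.0 | 0.0 | 70.4 | 0.0 |
| +0.2 / −0.2 (f = 0.1) | 45.3% | 31.7 | 32.2 | 13.1 | 0.0 | 23.1 |

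The first four rows all have the same interaction of 0.8 SD, yet the paired-test patterns differ widely. In every row the between-group contrast had the wrong sign in 0.0% of trials with a significant interaction.

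The way the effect divides between the arms, including any shared rise, is assumed in every row. The documents give no expected placebo change.

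**The case against.** A reader might infer three stronger things, and the documents support none of them.

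- *That the plan abandons the randomised comparison.* It does not. Hypothesis 1 is tested by the interaction, which in this design is the randomised comparison of change. The paired tests are labelled post hoc and are meant only to interpret an interaction.
- *That the paired tests will often mislead.* Once the interaction is significant, a lone significant paired test pointed to the wrong sign in 0.0% of simulated trials. With an even split, every case in which both were significant was in opposite directions, which shows the sign plainly. The tests are sometimes uninformative; they do not often point the wrong way.
- *That false claims become common.* With no treatment effect and a shared drift of 0.3 SD, exactly one arm is significant in 50% of trials. This matters only to someone who ignores the interaction test, which is significant in about 5% of those trials. The wording implies, without quite stating, that the paired tests follow a significant interaction.

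It is also fair to say that each paired t-test comes with a mean change. Subtracting the two gives the unadjusted interaction contrast, so a careful analyst can recover the sign from the same output. This stands, but that subtraction is the method the plan should name. The plan names significance tests instead.

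Lastly, a CI for the contrast is detail that an article may leave to an analysis plan. That is so, but the point here is a method the article does state. The missing CI alone would be no finding.

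**Conclusion.** The point holds as one of interpretation. The plan takes the direction of its primary result from tests that do not compare the groups, although the model supplies the right quantity directly. Under the protocol's inputs, the significance pattern fails to give the sign in about 5% of significant interactions with an even split, and in about 70% if both arms share a rise of the size assumed. If the true effect were half as large and evenly split, neither test would be significant in about 23%. In the simplest pattern that fits the hypothesis, the paired tests behave as expected in about 96%. Type I error and power for Aim 1 do not change. For the cognitive measures the point applies only as far as the paired tests are carried over, which the text leaves open.

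**What to change.** Replace the sentence on paired t-tests. State that the direction and size of the effect are given by the istradefylline-minus-placebo difference in mean change, estimated from the same model and reported with its 95% CI. Show within-group mean changes with CIs descriptively, without using their significance to assign direction. Apply this to BP_ND and, where the same model is used, to the cognitive measures. The cost is a sentence or two in the analysis section; sample size, visits and trial conduct are unchanged. It should be settled before unblinding.
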